### 2.5. Study Specific Visits and Procedures

Each specific visit and measurement is summarized in Table 2. Baseline measures include fasting FSH, LH, total testosterone (T), estradiol (E2), sex hormone binding Globulin (SHBG), dehydroepiandrosterone sulfate (DHEAS), glucose and insulin concentrations, cholesterol, triglycerides, high-density lipoprotein cholesterol (HDL-C), low-density lipoprotein cholesterol (LDL-C) and height, weight, hip, waist measurements, and vital signs. Neither cervical mucus nor endometrial lining will be monitored in this large clinical trial as these are not routinely monitored in clinical practice. Also questionnaires for assessments of health related quality of life (QOL) are filled in: the short form 36 (SF 36) [33], the Polycystic Ovary Syndrome Questionnaire (PCOS-QOL) [34], and the Chinese Quality of life (ChQOL) [35]. Questionnaires for symptoms of anxiety and depression are Zung Self-Rating Anxiety Scale (SAS) [36] and Zung Self-reported Depression Scale (SDS) [37]. All questionnaires used in this trial are validated scales. 

The TCM diagnosis will be made by an experienced TCM doctor in each participating site according to a standard questionnaire. Syndrome differentiation in TCM is the comprehensive analysis of clinical information gained by the four main diagnostic TCM procedures: observation, listening, questioning, and pulse analysis [38]. In PCOS, patients are empirically differentiated to be four categories: (1) phlegm-dampness syndrome, (2) blood stasis syndrome, (3) phlegm and blood stasis, and (4) liver stagnation [39]. The TCM diagnosis will not affect the treatment protocol, and it will enable us to explore its effect on the treatment success in a secondary analysis.

All baseline measures will be repeated in all subjects at the end of visits. Blood samples (including the safety labs) will be collected and shipped to the core lab. Credibility check questionnaires are completed on the third acupuncture treatment and the last acupuncture treatment [40–42].

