### 2.9. End of Treatment Visit

At the end of study, a visit will be arranged for all women. The end of treatment visit should be performed as early as possible in pregnant women. A brief physical examination including acne and hirsutism assessment and a final assessment of adverse events and concomitant medications will be performed. Subjects will return the remaining study drug and their journal logs. All baseline measures will be repeated in all subjects. 

The blood samples done at the baseline visit and the end of the treatment visit will be shipped to the core laboratory for analysis. 

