### 2.12. Data Analysis

The primary outcome is the live birth rate. Secondary outcomes include (1) ovulation rate; (2) ongoing pregnancy rate at gestation 8–10 weeks; (3) multiple pregnancy rate; (4) miscarriage rate: loss of an intrauterine pregnancy before 20 completed weeks of gestation; (5) change in hormonal profile: FSH, LH, T, SHBG, and DHEAS; (6) change in metabolic profile: glucose and insulin concentrations, cholesterol, triglycerides, HDL-C, and LDL-C; (7) side effect profile; (8) change in QOL; (9) change in symptoms of anxiety and depression; and (10) credibility assessments.

The analysis will use an intent-to-treat (ITT) approach to examining differences in the live birth rates among the four treatment arms. Primary efficacy analysis will be done by comparing the treatment groups with respect to the primary outcome of live birth using the Pearson Chi-square test. For the secondary, supportive analysis, we will fit a logistic regression model to compare the treatment arms with respect to the primary outcome of live birth, adjusting for other factors such as randomization stratification of study site and prior exposure to study medications. The analysis of other secondary outcomes measured over time will entail the application of statistical methods that have been developed for correlated data since repeated observations will be made over time on each individual. For secondary outcomes such as hormone levels, a linear mixed-effects model will be fit where the main independent variables will be treatment group, time, and their interaction as well as the designed randomization stratification factors as covariates. Logistic regression models will be used in secondary analyses to evaluate the predictive value of treatment arm, clinical site, prior exposure to CC, body mass index, and other explanatory variables on binary outcomes (e.g., singleton live birth, abortion). Cox proportional hazards models and a Kaplan-Meier method will be applied to compare time to pregnancy in the treatment groups. 

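### Hormonal and metabolic change is compared across arms with end-of-treatment samples that include pregnant women, so the contrast is a total effect including pregnancy and not by itself an effect on the PCOS profile

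*Protocol article*

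**What the plan says.** Section 2.5 fixes who is measured: "All baseline measures will be repeated in all subjects at the end of visits". Section 2.9 repeats this for all women and sets the timing for those who conceive: "The end of treatment visit should be performed as early as possible in pregnant women". It also names the samples used: "The blood samples done at the baseline visit and the end of the treatment visit will be shipped to the core laboratory for analysis". Table 2 marks fasting blood for study parameters at baseline and at end of treatment, and nowhere between.

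Section 2.12 lists among the secondary outcomes "change in hormonal profile: FSH, LH, T, SHBG, and DHEAS" and "change in metabolic profile: glucose and insulin concentrations, cholesterol, triglycerides, HDL-C, and LDL-C". For outcomes such as hormone levels, "a linear mixed-effects model will be fit where the main independent variables will be treatment group, time, and their interaction", with the randomization stratification factors as covariates. Pregnancy status is not among the named terms. Under Section 2.6, responders are treated until they conceive or complete four cycles. Table 3 projects live birth rates of 25% (A), 15% (B), 15% (C) and 5% (D).

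**The concern.** A woman who conceives contributes a follow-up value drawn while pregnant, and drawn sooner after baseline than the values of women who complete four cycles. If early pregnancy shifts a marker, each arm's mean change contains that shift in proportion to its share of pregnant women. The trial's own projections make those shares unequal. The arm-by-time term then adds together any effect on the endocrine or metabolic profile and the effect of being pregnant.

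The Introduction motivates the trial partly with earlier reports that acupuncture lowered testosterone and the LH/FSH ratio, so readers will probably set the hormonal results beside those reports. An arm that only produced more pregnancies could then appear to have changed the hormonal profile.

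**Working it through.** The plan gives no effect size or power for these secondary outcomes, so there is no figure of its own to reproduce on this point. The effective sample does reproduce: 250 × (1 − 0.20) = 200 per arm.

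**Inputs**
- Live birth rates 25%, 15%, 15%, 5%: Table 3.
- Pregnancy-to-birth ratio 36/29 = 1.24: the six-month clomiphene figures in the Introduction. Applying it to all four arms is an assumption.
- n = 200 per arm: Section 2.11.
- Shift k in a marker caused by pregnancy, in SD of the change score: not in the document. Assumed range 0.25 to 2.

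**Formulas**, with q the pregnant share in an arm and no treatment effect in non-pregnant women:
- Difference in mean change = k(q₁ − q₂).
- Variance per woman = 1 + k²q(1 − q), which allows for mixing pregnant and non-pregnant women.
- SE = √[(v₁ + v₂)/200].
- Chance of two-sided p<0.05 = Φ(d/SE − 1.96) + Φ(−d/SE − 1.96).

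**Worked case: live birth rates as q, k = 1**
- A-B: d = 0.10; v = 1.1875 and 1.1275; SE = 0.108; chance 15%.
- C-D: d = 0.10; v = 1.1275 and 1.0475; SE = 0.104; chance 16%.
- A-D: d = 0.20; v = 1.1875 and 1.0475; SE = 0.106; chance 47%.
- B-C: d = 0, because both rates are 15%; chance 5%, the nominal level.

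Live birth rates understate the pregnant share. Multiplying by 36/29 gives 31.0%, 18.6%, 18.6% and 6.2%.

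| k (SD) | q used | A-B | C-D | A-D |
|---|---|---|---|---|
| 0.25 | live birth | 6% | 6% | 8% |
| 0.25 | × 36/29 | 6% | 6% | 10% |
| 0.5 | live birth | 8% | 8% | 17% |
| 0.5 | × 36/29 | 9% | 9% | 23% |
| 1 | live birth | 15% | 16% | 47% |
| 1 | × 36/29 | 21% | 22% | 64% |
| 2 | live birth | 35% | 41% | 91% |
| 2 | × 36/29 | 47% | 55% | 98% |

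**Precision of the stated model.** With two time points and free baseline means, the arm-by-time term is a comparison of change scores. Taking equal variances at the two visits and correlation ρ, the variance is proportional to 2(1 − ρ). With a common baseline mean, or ANCOVA on baseline, it is 1 − ρ². The ratio is (1 + ρ)/2: 0.65 at ρ = 0.3, 0.75 at 0.5 and 0.85 at 0.7, so the variance is 35%, 25% and 15% lower. This gain is separate from the pregnancy question and does not resolve it.

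**The case against.** The strongest reply is that nothing here is invalid. Change that comes about through conception is a consequence of randomized treatment, so the comparison of all women estimates a genuine total effect. A reader might infer that the plan has an inflated type I error. That does not follow: the percentages above are error rates only if the contrast is read as an effect in women who are not pregnant. This objection stands, and it limits the point to labelling and interpretation.

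A reader might also infer that the plan itself makes a mechanistic claim. It does not. The three hypotheses in the Introduction concern live birth, and hormonal change is listed without any such claim.

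Another tempting reading is that samples from pregnant women should be set to missing in the main analysis. The document does not support that either. With only two samples, a woman who conceives would have no follow-up value, and the contrast would rest on women who never conceived, a group selected after randomization. If women with a better endocrine response conceive more often, missing at random given baseline and arm fails.

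Extending the point to quality of life and mood is not supported. For an infertility treatment, an improvement that comes from conceiving may be part of the benefit, and the explicit model is given for outcomes such as hormone levels.

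Finally, an analysis plan that is not shown may handle pregnancy, and the early visit limits gestation at sampling. Both are fair. But the article itself fixes who is sampled, when, and the model's main terms, and an early sample is still drawn in pregnancy.

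**Conclusion.** The point holds for hormonal and metabolic change as a matter of what the contrast means. As written, it is a total effect that includes pregnancy, and it cannot by itself support a statement about the PCOS profile.

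The size is uncertain because the document gives no marker shift. It is negligible for markers that early pregnancy barely moves and material for those it moves by about 1 SD or more. The largest figures are for A-D, which is not one of the three hypothesized contrasts. Among those three, A-B and C-D are affected, and B-C is not under Table 3. The calculation assumes the projected rates, 200 women per arm and one common shift across arms. The primary outcome of live birth is untouched.

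**What to change.** 1. In the hormonal and metabolic mixed model, constrain the arms to a common baseline mean, or use ANCOVA on baseline. Randomization justifies this, it lowers the variance by 15% to 35% for ρ from 0.7 to 0.3, and it has no real downside.

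2. Label the contrast in all women as a total effect that includes pregnancy. Prespecify a supplementary analysis that treats conception, dated by the first positive weekly hCG, as an intercurrent event and omits values drawn after it. State its missing-at-random assumption. Make no claim of an effect on the endocrine profile unless both analyses agree.

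The cost is wording and one extra analysis. Weekly hCG is already collected (Section 2.8, Table 2), and Section 2.12 places unblinding after final outcomes apart from medical emergencies, so the rule can be set while the arms are masked. The supplementary analysis loses roughly 5% to 31% of follow-up values by arm (D on the live birth rate, A on the scaled pregnancy rate). Agreement between the two analyses supports an endocrine reading but does not prove it, since the missing-at-random assumption cannot be tested with these data.

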### 2.10. Establishment of a Pregnancy Registry

The outcomes of all pregnancies will be followed after delivery or termination of gestation. We will review pregnancy and birth records of the mother and of the fetus to establish neonatal morbidity and mortality and the presence of fetal anomalies. We will extract from these records concomitant medical and obstetrical conditions, exposure information on all other medical products used, including prescription products, over-the-counter products, dietary supplements, vaccines, and insertable or implantable medical devices. We will file individual case reports for all congenital anomalies, which will be reported as serious adverse events. The ectopic pregnancies will be identified by serial hCG monitoring and pelvic ultrasound examination. The doctors performing pelvic ultrasound are blinded to the treatment groups.

### 2.11. Sample Size Calculations

The overall live birth rate for women to receive CC is estimated to be 20% during the 4-month period according to Chinese Obstetrics and Gynecology (Second Edition). Due to lack of existing data on the effectiveness of acupuncture, we cannot rely on the literature for samples size determination. Instead we hypothesize that the order of effectiveness of the treatments is as follows: True acupuncture and CC > Control acupuncture and CC,  control acupuncture and CC > True acupuncture and placebo CC,  true acupuncture and placebo CC > Control acupuncture and placebo CC. The respective live birth rates are projected with 10% difference as follows and the average rate among four arms is 15% (Table 3).

 Using a two-sided trend test and with an effective sample of 200 per group, our study is designed to have >80% power at the significance level of 0.015 (we have three primary hypotheses). The sample size has been inflated from 200 to 250/arm to allow for a dropout rate of 20%, totally 1000 cases for four arms. 

There have been multiple trials to study the effects of CC in PCOS women. The primary aim of this trial is not to reassess the efficacy of CC. The aim is to elucidate the additional efficacy of acupuncture in combination with CC, or acupuncture alone. Acupuncture is compared with CC because CC has been demonstrated to be superior to metformin [4]. The previous study design is used as a role model since it was the best executed and most cited trials in this area. [name] chairs the Steering Committee of this trial, and [name] leads the DCC for another trial using CC in PCOS women. They have considered all related studies, although the power calculation involved inevitably some assumptions. The significance level of 0.015 is approximately 0.05/3 because in this study the overall significance level is controlled to 0.05 after correcting for the multiple comparisons involving three primary hypotheses.

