## 1. Introduction

Polycystic ovary syndrome (PCOS) is the most common endocrine disorder in women of reproductive age. It is characterized by ovulatory dysfunction, hyperandrogenism, and polycystic ovaries (PCO) and affects 5–10% of premenopausal women [1]. In addition to irregular menses, hirsutism, and infertility, women with PCOS may display a number of metabolic abnormalities including hyperinsulinemia, insulin resistance, dyslipidemia, and obesity [2]. Clomiphene citrate (CC) is considered as the first line treatment to induce ovulation in women with PCOS. A compilation of published results from 5,268 patients revealed an ovulation rate of 73% per cycle per patient, pregnancy rate of 36% per patient, and live birth rate of 29% per patient during a six-month treatment [3]. Women who do not ovulate while receiving the maximum 150 mg dose are considered to be CC resistant and those who do not conceive after an ovulatory response are considered clomiphene failures. Both appear to be common [4], necessitating the search for adjuvant therapies to treat infertility in women with PCOS. 

Inability of CC to induce ovulation is more likely in patients who are obese, insulin resistant, and hyperandrogenic compared with those who do respond [5]. The mechanism of CC failures may partly be explained by a peripheral anti-estrogenic effect at the level of endometrium and cervical mucus or by hypersecretion of luteinizing hormone (LH). Side effects of CC are related to its combined estrogenic and antiestrogenic properties, which include hot flushes, breast discomfort, abdominal distension, nausea, vomiting, nervousness, sleeplessness, headache, mood swings, dizziness, hair loss, and disturbed vision [4]. Approximately 7% of pregnancies resulting from CC-induced ovulation are twin pregnancies and 0.5% are triplet pregnancies [6]. 

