Three control procedures are commonly used in acupuncture clinical trials: waiting-list, nonpenetrating needle, and needle-insertion (superficial or deep) controls. Waiting-list control was more frequently used in earlier RCTs. Nonpenetrating sham needle control, also known as “placebo control,” with a device that looks and feels like a real acupuncture needle but has a blunted tip that retracts into a hollow shaft handle and touches the skin without penetration [48] and needle-insertion control, with superficial needle placement at acupuncture points or at nonpoint or “wrong” point, or deep needle placement at “wrong points” [49, 50] are all frequently used control situations. Importantly, none of these control procedures are inert. As previously mentioned, the design of true acupuncture is based on existing data from experimental studies, on a previous RCT in PCOS women [20], and on an unpublished RCT registered at ClinTrial.gov (NCT00921492). 

The control acupuncture is chosen in contrast to true acupuncture and designed in such way that we believe it is least effective. The needles used in control acupuncture, which are thinner and shorter than those in true acupuncture, are inserted superficially in the skin without any stimulation, one in each shoulder and on in each upper arm at nonacupuncture points. Placement of needles in the control acupuncture is unlikely to induce ovulation in women with PCOS. The electrodes are attached to the needles but without any stimulation in order to mimic EA in the true acupuncture. The use of control acupuncture is not only to keep the study investigators (except the acupuncturists) blinded to the treatment but also to let the participants know that a certain acupuncture was performed to minimize the bias of the psychological effects receiving or not receiving a perceived effective acupuncture treatment. The participants are informed that two acupuncture protocols are tested, but they do not know which one is better in achieving ovulation and live birth. 

We have further created a unique study team consisting of experts in Western and TCM, clinical trials, biostatistics, and ethics, and developed a multilanguage infrastructure to conduct and monitor the trial. This model both serves to provide additional oversight and quality control to the trial but also allows for the mutual education of all participating investigators in areas where their previous training or experience was limited. 

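### Table 3 plans clomiphene plus control acupuncture (arm B) at 15%, five points below the plan's own 20% clomiphene rate, without explanation; pairwise power for hypothesis 1 is 53% as planned and 45% with the cited rate

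*Protocol article*

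**What the plan says.** Section 2.11 opens the sample size argument with an external figure: "The overall live birth rate for women to receive CC is estimated to be 20% during the 4-month period according to Chinese Obstetrics and Gynecology". It then says that the literature gives no usable data on how effective acupuncture is, and that an ordering of the four arms is hypothesised instead. On the rates themselves it says: "The respective live birth rates are projected with 10% difference as follows and the average rate among four arms is 15" (per cent).

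Table 3 gives A (true acupuncture + CC) = 25%, B (control acupuncture + CC) = 15%, C (true acupuncture + placebo CC) = 15% and D (control acupuncture + placebo CC) = 5%.

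The power statement reads "Using a two-sided trend test and with an effective sample of 200 per group", followed by "our study is designed to have >80% power at the significance level of 0.015 (we have three primary hypotheses". The allowance for dropout is: "The sample size has been inflated from 200 to 250/arm to allow for a dropout rate of 20" (per cent).

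Three other places bear on the point. The Introduction states three pairwise hypotheses: A better than B, B better than C, and C better than D. Section 2.12 names the Pearson chi-square test for the primary analysis. The Discussion says of the control procedure: "Placement of needles in the control acupuncture is unlikely to induce ovulation in women with PCOS".

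**The concern.** The 20% is a rate on CC. Since section 2.11 says that acupuncture data are lacking, it cannot be read as a rate on CC combined with true acupuncture. The control needling is expected to do little, so arm B is the arm that the figure describes. Table 3 puts that arm five points lower, and nothing in the article suggests that control needling reduces the chance of a live birth.

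Two things are at stake. First, the comparator rate sets the variance of a binary comparison. For a fixed 10-point difference in this range, a higher comparator rate means lower power for A versus B, the comparison that addresses the added benefit of acupuncture on top of CC. Second, the target becomes ambiguous. Arm A at 25% is 10 points above Table 3's arm B but only 5 points above the cited CC rate, and a null result for A versus B means different things in the two cases.

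**Working it through.** **Inputs.** CC rate 20% over 4 months, 200 evaluable per arm and two-sided alpha 0.015 (section 2.11); rates 25/15/15/5% for A/B/C/D (Table 3); Pearson chi-square (section 2.12); pairwise hypotheses (Introduction).

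**Step 1. Where the 20% sits in Table 3.** No cell holds 20%. The mean of the CC row is (25 + 15)/2 = 20%. The four-arm mean is (25 + 15 + 15 + 5)/4 = 15%, as printed.

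**Step 2. Reproduce the plan's own figures.** Dropout: 200/(1 − 0.20) = 250 per arm, as stated. Trend test: Cochran-Armitage with centred scores w, T = Σ w·p, s0 = √[p̄(1 − p̄)Σw²/n], s1 = √[Σw²p(1 − p)/n], power = Φ((T − 2.432·s0)/s1). The article does not give the scores. With 3-2-1-0 and Table 3: T = 0.300, s0 = 0.0565, s1 = 0.0544, so the power is Φ(2.99) = 99.9%. With 2-1-1-0 it is above 99.9%. The printed claim of more than 80% is met.

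**Step 3. Does the trend-test figure survive the corrected rates?** With scores 3-2-1-0:

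- 30/20/15/5%: above 99.9%
- 30/20/20/10%: 99.1%

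It does, under either set.

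**Step 4. Pairwise power, two-sided 0.015, n = 200 per arm.** s0 = √[2p̄(1 − p̄)/n], s1 = √[(p₁(1 − p₁) + p₂(1 − p₂))/n], power = Φ((|p₁ − p₂| − 2.432·s0)/s1).

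*Hypothesis 1, A versus B*

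- Table 3, 25% vs 15%: s0 = 0.0400, s1 = 0.0397; Φ(0.068) = 52.7%
- B at the cited rate with the 10-point effect kept, 30% vs 20%: s0 = 0.0433, s1 = 0.0430; Φ(−0.124) = 45.1%
- The variance sum p₁(1 − p₁) + p₂(1 − p₂) rises from 0.315 to 0.370 (0.370/0.315 = 1.17), and n for 80% power rises from 342 to 401 evaluable per arm
- Simulation of the Pearson test gives 53.4% and 45.7%, so the approximation is adequate

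*Hypothesis 2, B versus C*

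- Table 3, 15% vs 15%: no planned difference
- 20% vs 15% (C kept): 13.2%
- 20% vs 20% (C moved up as well): again no planned difference

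*Hypothesis 3, C versus D*

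- 15% vs 5% (Table 3, or C and D kept): Φ(0.914) = 82.0%
- 20% vs 10% (both moved up by five points): Φ(0.372) = 64.5%

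**Step 5. Four-arm average after correction.** (30 + 20 + 15 + 5)/4 = 17.5%; (30 + 20 + 20 + 10)/4 = 20%.

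**Side check.** The Introduction reports a "live birth rate of 29% per patient during a six-month treatment" on CC. Assuming a constant monthly rate, that is 1 − 0.71^(4/6) = 20.4% over four months. The article gives no support for a constant rate, and the dose is stepped up in non-responders, so this is only loosely consistent with 20% and carries no weight in the conclusion.

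**The case against.** The strongest reply is that Table 3 is presented as a hypothesised projection and not as a derivation from the textbook. Section 2.11 says the literature cannot be relied on for acupuncture and concedes that assumptions were unavoidable. The table is internally regular: 10-point steps along rows and columns and a correct mean of 15%. This stands as a reason not to call it an arithmetic error. It does not explain why a CC rate is cited and the CC comparator is then planned below it.

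A reader might infer more than the document supports, in four ways.

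- **That the stated power is overstated.** The only printed power is for the trend test, and it stays at 99% or more. The acupuncture main effect (400 versus 400, at 0.015) also stays above 80%: 93.9% with Table 3, and 90.3% and 86.7% under the two corrected sets. No power is printed for A versus B alone.
- **That the low power for A versus B comes from this input.** Most of the gap to 80% is already there with Table 3's own rates (52.7%), because power was stated for a trend test while the hypotheses are pairwise. The input accounts for about 8 points (52.7 − 45.1 = 7.6).
- **That the CC rate was certainly averaged over both CC arms.** This is inferred from the row mean and from the word overall; the article does not say it.
- **That hypothesis 3 drops below 80%.** It does so only if C and D move to 20% and 10%. A CC rate says nothing about the placebo-CC arms, and no section supports those values. If C stays at 15%, hypothesis 2 gains a planned difference, so the correction does not work in one direction only.

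**Conclusion.** The concern holds as an unexplained conflict between a cited planning rate and its use. Arm B is planned five points below the plan's own 4-month CC rate, although its needling is expected to have little effect. The printed trend-test power is unaffected.

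For hypothesis 1 the consequence is pairwise power of 45% in place of 53%, given 200 evaluable per arm, two-sided 0.015, a Pearson chi-square test and a 10-point effect kept at 30% versus 20%. If A were left at 25% against B at 20%, power would be 10.8%, but that gives up the plan's 10-point effect and is shown only as the other end of the range. The consequences for hypotheses 2 and 3 depend on C and D rates that the document does not source.

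**What to change.** In section 2.11 and Table 3:

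1. Set arm B to the cited 20%, with A = 30% if the 10-point effect is kept, or give the reason for planning arm B at 15%.
2. State the C and D rates as assumptions.
3. Correct the four-arm average: 17.5% if C and D stay at 15% and 5%, 20% if they become 20% and 10%.
4. State the power of each pairwise hypothesis at 200 per arm and two-sided 0.015. Hypothesis 1: 45%. Hypothesis 2: 13% if C = 15%, no planned difference if C = 20%. Hypothesis 3: 82% if C and D are 15% and 5%, 64.5% if they are 20% and 10%.

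The change is to wording and one table. Enrolment and conduct stay as they are. The downside is a less favourable stated power for the pairwise hypotheses.
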